## Abstract

**Background:**

Sepsis is a dysregulated response of the host to infection that can lead to life-threatening organ dysfunction and remains a leading cause of mortality. Early recovery of impaired organ function is crucial for the outcomes of sepsis. Electroacupuncture (EA) is a promising adjunctive therapy for sepsis, but no study has focused on the efficacy of EA for organ dysfunction. This study aimed to investigate the efficacy and safety of EA in improving organ dysfunction among intensive care unit (ICU) patients with sepsis.

**Methods:**

In this single-center, randomized, sham-controlled clinical trial, an adaptive sample size of 154–500 patients diagnosed with sepsis will be included. Eligible patients will be randomly assigned to receive EA or sham EA treatment at a 1:1 ratio using block randomization. Patients in the two groups will receive 6 consecutive sessions of 30-min EA or sham EA treatment, with the initial acupuncture treatment being completed within 24 h after randomization. The primary outcome is the change in the total score of the Sepsis-Related Sequential Organ Failure Assessment (SOFA) on day 7 after randomization compared with baseline. Secondary outcomes include changes in the SOFA score and related serological outcomes, mortality, ICU-free days, hospital-free days and organ support-free days from baseline to day 28. Statistical analyses will be performed on a full analysis set (FAS) and a per-protocol set (PPS).

**Discussion:**

We expect the findings of this trial to provide evidence that the use of EA as an adjunctive therapy to ICU treatment can promote the recovery of organ function and other outcomes in sepsis patients.

**Trial Registration:**

ClinicalTrials.gov identifier: NCT06666946. Registered on 28 October 2024.

**Supplementary Information:**

The online version contains supplementary material available at 10.1007/s11596-026-00225-5.

## Introduction

Sepsis is a life-threatening condition characterized by a dysregulated response to infection and can lead to multiorgan dysfunction or septic shock [1]. It is a major cause of mortality, and the latest Global Burden of Disease Study reported 11.0 million sepsis-related deaths in 2017, representing 19.7% of all global deaths [2]. Moreover, sepsis imposes a significant burden on healthcare systems worldwide, with approximately half of sepsis patients receiving intensive care unit (ICU) care [3]. In China, sepsis is associated with an increasing burden of hospitalizations and affects one-fifth of patients admitted to ICUs [4, 5]. Therefore, the World Health Organization (WHO) considers sepsis a global public health priority [6].

The underlying mechanisms of sepsis involve excessive inflammation and immune suppression, resulting in multiorgan dysfunction or even septic shock [7, 8]. Although numerous interventions targeting the attenuation of inflammation or the removal of inflammatory mediators, such as glucocorticoids, vitamin C and some new targeted drugs, have shown promise in theory, most randomized controlled clinical trials (RCTs) have failed to demonstrate significant reductions in mortality or improvements in other clinical outcomes of sepsis [9–18]. Sepsis patients rarely exhibit single-organ dysfunction; instead, they typically progress to multiple-organ failure, in which the severity strongly correlates with the mortality of sepsis [19]. However, most sepsis-induced organ dysfunction is reversible [20]. Thus, the development of new therapies to prevent or mitigate organ dysfunction and prevent cytokine storms caused by sepsis is highly necessary.

Acupuncture has emerged as an adjunctive therapy for sepsis because of its potential efficacy in reducing inflammation or facilitating immune normalization [21–23]. Electroacupuncture (EA) is an adaptation of traditional acupuncture, and the core mechanism through which EA is used to treat various diseases is the delivery of controlled electrical pulses through fine needles inserted at specific acupuncture points. Notably, the use of acupuncture and EA is currently transitioning from empirical medicine to evidence-based medicine [24]. Recently, a study published in Neuron demonstrated that low-intensity EA can effectively inhibit excessive inflammatory responses and reduce the 7-day mortality rate by approximately 40% [25]. A subsequent study published in Nature further confirmed that this effect is mediated through the “PROKR2^ADV^ fibers-vagus nerve-adrenal NPY^+^ chromaffin cells” pathway [21]. These seminal findings indicate the promising role of EA as an adjunctive therapy for sepsis. In addition, several small-sample clinical trials have provided preliminary evidence supporting the efficacy of EA for sepsis [23]. However, limited evidence has supported the efficacy of EA for preventing organ dysfunction induced by sepsis. Therefore, this trial aimed to investigate whether EA, as an adjunctive treatment to standard-of-care therapy, can promote the recovery of organ function and other outcomes of sepsis patients in the ICU. The study protocol is designed in response to the core recommendations of the Rome Consensus on Good Clinical Trials for Traditional Medicine [26].

## Methods and Analysis

### Study Design

This is a single-center, randomized, participant- and outcome-assessor-blinded, sham-controlled, clinical study. The study will be conducted at the Tongji Hospital, affiliated with Tongji Medical College, Huazhong University of Science and Technology (HUST) in Wuhan, China. An adaptive sample size of 154–500 patients will be recruited from the ICU ward within 24 h of their ICU admission. The total trial period comprises 24 h of baseline assessment, 6 days of postrandomization treatment, and a 22-day follow-up period. Written informed consent will be obtained before randomization. ICU-attending physicians will provide detailed informed consent to patients or their legal guardians under ICU monitoring. Upon confirmation of eligibility, patients will be randomized into either the EA group or the sham-EA group. A complete treatment protocol requires the following: (1) the initial acupuncture treatment should be administered within 12 h post-randomization, and (2) six sessions of EA or sham EA should be conducted once daily for 30 min per session. The study protocol strictly adhered to the Standard Protocol Items: Recommendations for Interventional Trials (SPIRIT) reporting guideline [27]. The trial flowchart is presented in Fig. 1, with detailed procedures and schedules outlined in Table 1.

**Fig. 1 Fig1:**
[figure not shown]
Study flow diagram

**Table 1 Tab1:** Schedule of recruitment, interventions, and measures

	Time point (days)											
	Baseline		Treatment						Follow-up			
	–1	0	1	2	3	4	5	6	7	8	9	28
**Enrollment of sepsis patients**												
Screening	** × **											
Informed consent	** × **											
Demographic characteristics	** × **											
Previous disease history	** × **											
Physical examination	** × **											
**Randomization**		** × **										
**Intervention**												
EA group			** × **	** × **	** × **	** × **	** × **	** × **				
Sham EA group			** × **	** × **	** × **	** × **	** × **	** × **				
**Measures**												
SOFA score	** × **		** × **	** × **	** × **	** × **	** × **	** × **	** × **	** × **	** × **	
SOFA score of each system	** × **		** × **	** × **	** × **	** × **	** × **	** × **	** × **	** × **	** × **	
SOFA score components	** × **		** × **	** × **	** × **	** × **	** × **	** × **	** × **	** × **	** × **	
All-cause (ICU) mortality												** × **
ICU/hospital-free days												** × **
Ventilator-free time												** × **
Vasopressor-free days												** × **
CRRT-free days												** × **
Liquid equilibrium parameter	** × **		** × **	** × **	** × **	** × **	** × **	** × **				
Serum biomarkers and related cellular assays	** × **				** × **				** × **			
AEs			** × **	** × **	** × **	** × **	** × **	** × **				

EA, electroacupuncture; SOFA score, Sequential Organ Failure Assessment score; ICU, intensive care unit; CRRT, continuous renal replacement therapy; AEs, adverse events

### Eligibility Criteria

#### Inclusion Criteria

Eligibility patients have to meet the following inclusion criteria: 1) 18 years or older, no restriction on sex; 2) diagnosis of sepsis on the basis of Sepsis-3 criteria: an increase in the Sepsis-Related Sequential Organ Failure Assessment (SOFA) score by more than 2 points from baseline in the context of confirmed or suspected infection [1]; and 3) the patient or their legal guardian having the ability to understand the informed consent form and willingness to sign it.

#### Exclusion and Shedding Criteria

Patients who met any of the following criteria were excluded: (1) lower extremity denervation; (2) lower extremity amputation or congenital limb hypoplasia; (3) severe acute trauma to the lower extremities, including active bleeding or unstable fractures; (4) skin damage, infection, bleeding, or hematoma near the acupuncture site on the lower extremities; (5) the presence of implantable medical devices, such as pacemakers, implantable cardioverter defibrillators (ICDs), or deep brain stimulators (DBSs); (6) pregnancy or breastfeeding; (7) an expected ICU stay of less than 48 h; (8) opting for palliative care instead of active treatment; (9) concurrent participation in another RCT; (10) refusal or inability to provide informed consent; (11) immunosuppressive status, including congenital immunodeficiency, acquired immune deficiency syndrome (AIDS), organ transplantation, long-term immunosuppressant use, or tumor radiotherapy/chemotherapy within 1 month; and (12) ICU physician evaluation indicating an anticipated survival prognosis of less than 7 days, making completion of the acupuncture treatment course unfeasible.

### Randomization and Allocation Concealment

Eligible participants will be randomly assigned to the EA group or the sham-EA group at a ratio of 1:1 through dynamic block randomization. Computer-generated randomization sequences will be produced by an independent investigator and secured in sequentially numbered, opaque, sealed envelopes. Afterward, a nonblinded acupuncturist will access the allocation assignment by opening envelopes in sequential order and subsequently administering the corresponding intervention. To maintain blinding in patients, outcome assessors, and statisticians, the allocation sequence will be concealed until the end of the study.

### Blinding and Masking

In this study, participants and outcome assessors will be blinded to group assignment. To ensure this, we will establish standard EA procedures to ensure that both groups receive identical treatment protocols (e.g., acupuncture time, frequency, and manipulation). Participants will undergo EA treatment and outcome assessments at separate times each day. Acupuncturists will be instructed not to reveal the patients’ group allocation to the outcome assessor and will sign confidentiality agreements. As acupuncturists perform acupuncture by manipulating needles, masking them is not feasible. Given that sepsis patients often have altered mental status, assessment of patient blinding is not applicable to this study.

### Interventions

The treatment protocol was developed with reference to studies published in *Nature*, *Neuron*, and related clinical research literature, incorporating the opinions of experts in acupuncture and critical care. A detailed list of the experts is provided in supplement 1 (Table S1). EA or sham EA treatment will be performed by qualified acupuncturists, who have a traditional Chinese medicine (TCM) certificate, and who will independently perform clinical treatment for more than two years. Before the treatment begins, acupuncturists should have undergone centralized training to ensure uniformity in the acupuncture procedures. EA conditions and adverse reactions will be recorded after each EA or sham EA on the acupuncture record form. Details of the procedures for the EA group and the sham EA group are presented in Fig. 2.

**Fig. 2 Fig2:**
[figure not shown]
The acupoints and operation methods of the EA group and Sham EA group

#### EA Group

Participants in the EA group will receive acupuncture at bilateral acupoints ST36 and GB34. In patients in the supine position, after sterilization, sterile adhesive pads will be placed on the bilateral ST36 and GB34. Afterward, the acupuncturist inserted sharp needles into the skin of acupoints ST36 and GB34 approximately 20 to 30 mm through the adhesive pads, followed by manual manipulation of each needle for 10 s to induce sensation of deqi (a composite of sensations including soreness, numbness, distention, heaviness, and other sensations). Afterward, paired electrodes from the EA apparatus will be attached transversely to the needle handles at bilateral ST36 and GB34. EA stimulation lasted for 30 min, with a continuous wave of 10 Hz and a current intensity of 1 mA (preferably with the skin around the acupoints shivering mildly without pain). Participants will receive EA sessions once daily for 6 consecutive days.

Sterile, disposable Hwato-type acupuncture needles (Suzhou Medical Supplies Factory Co., Ltd., China) 0.30 mm in diameter and 40 mm in length were used. EA stimulation was delivered using a Hwato SDZ‑V EA device.

#### Sham EA group

Participants in the sham EA group will receive sham EA with a noninsertive placebo needle on sham acupoints. The sham ST36/GB34 point is located at 1 cun (approximately 20 mm) lateral to acupoint ST36/GB34. The procedures, electrode placements, and other treatment settings will be the same as those in the EA group but with no skin penetration or electricity output*.*

#### ICU Standard Therapy

All participants received standard ICU therapy, which was developed on the basis of expert consensus [28]. Routine treatment includes source control of infection, antibiotics and/or other anti-infective measures, sedation and analgesia, fluid management, mechanical ventilation, renal replacement therapy, nutritional support and so forth. EA sessions will be scheduled within a flexible daily window, coordinated with bedside staff. Routine ICU care and emergency procedures take priority. If a session cannot be completed because of prone positioning or other interventions, it will be recorded as a protocol deviation.

#### Criteria for Discontinuing the Allocated Intervention

EA treatment can be ended if the following conditions occur: (1) The patient is excluded from the sepsis diagnosis during treatment because of concealment or failure to provide accurate medical information and past medical history by the patient or their family. (2) The patient experience serious adverse events during or after treatment. (3) The patient exhibit poor compliance or refuse to continue treatment.

### Study Endpoints

#### Primary Endpoint

In this study, ICU attending physicians who are blinded to treatment group assignments will be responsible for the outcome measures. The primary outcome of this study is the change in mean total SOFA score on day 7 after randomization compared with baseline (24 h before randomization). The SOFA score is a simple but effective method to describe organ dysfunction/failure in sepsis or other critically ill patients [29]. The scoring criteria for the SOFA score are detailed in supplement 1 (Table S2).

#### Secondary Endpoints

Participants will be followed up until day 28 after randomization. Secondary outcomes include the following: (1) all-cause mortality on day 28; (2) all-cause ICU mortality on day 28; (3) ICU-free days to day 28; (4) hospital-free days to day 28; (5) ventilator-free days to day 28; (6) vasopressor-free days to day 28; (7) continuous renal replacement therapy (CRRT)-free days to day 28; (8) changes in SOFA total scores at days 8 and 9; (9) changes in each item of the SOFA score (i.e., the ratio of arterial oxygen partial pressure to fractional inspired oxygen ratio (PaO_2_/FiO_2_), ventilator use, platelet counts, total bilirubin, mean arterial pressure, vasopressor use, Glasgow Coma Scale score, creatinine level, and urine volume) from baseline to day 9; (10) changes in serum biomarkers and related cellular assays on day 3 and day 7 compared with baseline; and (12) changes in the liquid equilibrium parameters, including daily fluid intake, output and fluid balance from baseline to day 6 after randomization.

### Safety Assessments

In reference to the literature concerning acupuncture-related adverse reactions, outcome assessors will record adverse events (AEs) during and after each treatment. The frequency of AE occurrence will be analyzed and evaluated. In this trial, AEs are defined as follows: (1) Any clinically significant adverse medical event occurring in patients receiving EA or undergoing study procedures that deviates from the expected clinical course of sepsis patients. (2) Any clinically significant adverse medical event considered related to EA or the study procedure, regardless of its alignment with the expected clinical course of sepsis patients. “Response to EA” refers to an adverse event for which a causal relationship with EA cannot be excluded.

In this study, acupuncturists evaluated the safety of acupuncture, and any AEs associated with acupuncture, including bleeding, subcutaneous hemorrhage, serious pain, local infection, and other unexpected adverse reactions, were documented. If AEs occur, the EA or sham EA ends, and experienced ICU doctors and acupuncturists promptly take necessary steps to ensure patient well-being.

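### The blinded outcome assessors are told to record adverse events during and after each session, which conflicts with the protocol's own safeguards for assessor blinding

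*Protocol article*

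**What the plan says.** Blinding and Masking states that "participants and outcome assessors will be blinded to group assignment". It gives two safeguards for the assessors. The first is separation in time: "Participants will undergo EA treatment and outcome assessments at separate times each day". The second is non-disclosure: acupuncturists must not reveal "group allocation to the outcome assessor and will sign confidentiality agreements". Primary Endpoint identifies the role: "ICU attending physicians who are blinded to treatment group assignments will be responsible for the outcome measures".

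Three statements then deal with adverse events:

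- Safety Assessments, first paragraph: "outcome assessors will record adverse events (AEs) during and after each treatment".
- Safety Assessments, second paragraph: "acupuncturists evaluated the safety of acupuncture", with needle-related events such as bleeding and subcutaneous hemorrhage documented.
- Interventions: "EA conditions and adverse reactions will be recorded after each EA or sham EA on the acupuncture record form".

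**The concern.** One role name carries two duties that pull against each other. Blinding and Masking keeps the outcome assessor's work apart from the session. Safety Assessments gives the outcome assessor a recording task tied to the session.

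The acupuncturists cannot be masked, as the article accepts, and patient blinding will not be assessed. Assessor blinding is therefore a main protection for the day-7 SOFA comparison. If the assessors can guess the arm, the items most exposed are the Glasgow Coma Scale, which is judged, and vasopressor and ventilator use, which follow care decisions. The secondary free-day endpoints depend on care decisions too, so far as the assessors have a part in them.

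**Working it through.** The point turns on who does what and when. The plan states no figure to reproduce, so the check compares the article's sections.

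**1. Is it the same role?** Blinding and Masking and Safety Assessments both say outcome assessors. Primary Endpoint gives the outcome measures to blinded ICU attending physicians. No section assigns adverse event recording to a differently named assessor.

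**2. Do the timings collide?** Table 1 schedules sessions on days 1 to 6, adverse events on days 1 to 6, and SOFA at baseline and on days 1 to 9. The assessor therefore has up to six session-linked recording occasions before the day-7 primary score.

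**3. What distinguishes the arms at or after a session?**

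| Feature | EA Group section | Sham EA group section | Could it reveal the arm? |
|---|---|---|---|
| Penetration | Sharp needle, 20 to 30 mm, through an adhesive pad | Non-insertive placebo needle, other procedures the same | Possibly hidden by pad and placebo needle |
| Current | 1 mA, "preferably with the skin around the acupoints shivering mildly without pain"; the Discussion also aims for slight needle tremor | No output | Yes, where movement is visible |
| Site | ST36 and GB34 | About 20 mm lateral | Possibly, to an observer who knows the points |
| Needle-site bleeding or haematoma | Expected mainly here | Less expected | Yes, even when seen only after the session |

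That bleeding or haematoma is expected mainly in the penetrating arm is inferred from the technique. The article does not state it.

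**4. Which outcomes are exposed?** Secondary Endpoints lists the SOFA items. Platelets, bilirubin, creatinine, PaO2/FiO2 and urine volume are laboratory or measured values and leave little room for judgement. The Glasgow Coma Scale is judged. Vasopressor and ventilator use follow care. A death within 7 days is scored 24 by rule, so it is not open to assessor judgement.

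**5. Is the assessor's presence needed?** The acupuncture record form already captures adverse reactions after each session, and acupuncturists already evaluate acupuncture safety. The assessor adds no procedural information that the form does not already collect.

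**6. Illustration only.** The bias values here are assumptions; none comes from the documents. With the plan's SD of 3.2 and N = 308, the standard error of the difference is 2 × 3.2 / √308 = 0.365. A bias b in favour of EA gives a one-sided type I error of 1 − Φ(1.96 − b/0.365):

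| Assumed bias b (SOFA points) | One-sided type I error |
|---|---|
| 0 | 2.5% |
| 0.1 | 4.6% |
| 0.2 | 7.9% |
| 0.3 | 12.8% |

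This uses a fixed-design cut-off and the unadjusted SD. The planned test is a weighted two-stage ANCOVA with a final one-sided level of 0.0245. The table shows only that a bias small beside the planned difference of 1.2 would matter. It does not show that such a bias exists.

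**The case against.** The strongest reply is that attendance is inferred. Recording events during and after treatment could mean logging events that fell in that window, from the chart or from the acupuncturist, without being at the bedside. On that reading the separation in time holds: acupuncturists handle procedural events and assessors collect general ones. This is a possible reading, but not the natural one, and the article does not say it. It also leaves the assessor receiving reports of needle-site bleeding or haematoma.

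A reader might infer several stronger things that the documents do not support:

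- **That assessors will see needles penetrate the skin.** Pads, placebo needles and matched procedures may hide this. Skin movement in the EA arm is described only as preferable.
- **That bleeding or haematoma occurs only with penetration.** No section says so; mainly is as far as one can go.
- **That the assessors control the same patients' vasopressors, ventilation, CRRT or discharge.** This is plausible from their post but not stated. Nor is it stated that whoever records a session's events also scores that patient on day 7, when no session is scheduled.
- **That the type I error rises by a known amount.** Every bias value is hypothetical.

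The conflict between the stated rule and the stated safeguard survives all of this. It is not a detail left to a fuller protocol or an analysis plan, because the article gives an explicit instruction that works against another.

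**Conclusion.** The concern holds as an internal contradiction that puts assessor blinding at risk. Safety Assessments gives the blinded role a session-linked task that Blinding and Masking is built to avoid, and the article names two different recorders for procedural events.

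It would be too strong to conclude that the trial is not assessor-blinded. That needs attendance at sessions, recognition of the cues, and the same person scoring SOFA, and the article establishes none of these outright. The size of any bias cannot be derived from the documents. Its likely location can: the Glasgow Coma Scale and care-driven items first, laboratory items least.

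The conclusion rests on two assumptions: that outcome assessor means the same role throughout, and that the phrase about recording during treatment carries its ordinary meaning.

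**What to change.** Reconcile Blinding and Masking, Interventions, Primary Endpoint and Safety Assessments so that they state one arrangement:

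1. Session-time and needle-site adverse events are recorded by the acupuncturist, or by another person who does not score SOFA, on the acupuncture record form.
2. SOFA assessors neither attend sessions nor see that form.
3. General adverse events are collected from the ICU record at the separate assessment time.
4. The sponsor documents who actually recorded session events for the 136 participants already enrolled (Trial Status). The archived video of more than 30% of sessions (Monitoring and Quality Control) may help show who was present, if someone who does not score SOFA reviews it.

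The cost is revised wording, an ethics resubmission (which Monitoring and Quality Control requires for a revised protocol) and brief retraining. No extra staff are needed if the acupuncturist keeps the form. There are two drawbacks. Procedural events would be ascertained by an unblinded person, which should be acknowledged when safety is reported; using a separate non-scoring recorder would avoid sole reliance on the acupuncturist. Also, a wording change cannot restore blinding for participants already treated. The 136 enrolled are 136/154 = 88% of the planned first stage, so item 4 is needed to show whether those data were affected.

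### Expectedness or judged relatedness decides whether an event counts as an adverse event, and the protocol does not say whether the blinded assessor or the unblinded acupuncturist makes that judgement

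*Protocol article*

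**What the plan says.** The Safety Assessments section defines an AE by two alternative limbs. The first admits a clinically significant event "that deviates from the expected clinical course of sepsis patients". The second admits "Any clinically significant adverse medical event considered related to EA or the study procedure, regardless of its alignment with the expected clinical course of sepsis". The frequency of AEs is then to be analysed.

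Two groups are given a part in the assessment:

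- The section first says that "outcome assessors will record adverse events (AEs) during and after each treatment". Blinding and Masking says that "participants and outcome assessors will be blinded to group assignment", and Primary Endpoint adds that "ICU attending physicians who are blinded to treatment group assignments will be responsible for the outcome measures".
- The next paragraph of Safety Assessments says that "acupuncturists evaluated the safety of acupuncture, and any AEs associated with acupuncture" were documented. The examples it gives are mainly local: bleeding, subcutaneous hemorrhage, serious pain and local infection, followed by a residual category of other unexpected reactions. On the acupuncturists, Blinding and Masking states: "As acupuncturists perform acupuncture by manipulating needles, masking them is not feasible".

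The Interventions section adds an acupuncture record form for adverse reactions after each session and does not name who completes it. No section says who decides that an event is unexpected for sepsis, or that it is related to the treatment or procedure.

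**The concern.** Expectedness and relatedness are normally recorded about an event that is already in the data. Here they decide whether the event enters the data. In septic ICU patients many systemic events fit the expected course, so they can count only if someone considers them related.

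Two things are at stake. First, a randomised sham arm allows a trial to see whether a common complication becomes more frequent under treatment without anyone deciding cause case by case. A definition that filters on cause first gives up that advantage for the filtered events, even if the person filtering is blinded. Second, if the filter is applied by someone who knows the allocation, the same event may be counted in one arm and not in the other. Safety is a stated aim in the Abstract and the Discussion, and AE frequency is the safety analysis named.

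**Working it through.** **Step 1. What the definition lets through.** Classify an event by whether it departs from the sepsis course and whether it is judged related.

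| Departs from sepsis course | Judged related | Counted as AE |
|---|---|---|
| yes | yes | yes |
| yes | no | yes |
| no | yes | yes, second limb only |
| no | no | no, in either arm |

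The last row is dropped whoever does the judging.

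**Step 2. Which dropped events are seen elsewhere.** Table 1 and Secondary Endpoints have SOFA total, system and component scores recorded daily to day 9 (including mean arterial pressure, vasopressor use, oxygenation, platelets, bilirubin, creatinine, urine volume and coma score). They also give all-cause mortality and ventilator-, vasopressor- and CRRT-free days to day 28. Hypotension and worsening organ failure are therefore measured in both arms whatever the AE label. Arrhythmia and bleeding away from the needle site are not among these outcomes.

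**Step 3. Who judges.** Blinded assessors record AEs; unblinded acupuncturists evaluate acupuncture safety. Under Randomization and Allocation Concealment, the acupuncturist opens the envelope and then treats, and the sham has neither penetration nor current. Blinding and Masking puts treatment and outcome assessment at separate times of day, yet the assessors are to record AEs during treatment. If the times are kept apart, an event during a session must reach the assessor through someone else, and the acupuncturist is an obvious source.

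**Step 4. Illustration of loss (assumed rates).** Arm size comes from Sample Size Calculation: 300 × 1.025 = 307.5, rounded up to 308, or 154 per arm. The documents give no AE rate. Suppose an uncaptured, sepsis-typical event occurs in 20% of sham and 30% of EA patients:

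- sham: 154 × 0.20 = 30.8, about 31
- EA: 154 × 0.30 = 46.2, about 46

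If all are called expected and unrelated, the record shows 0 and 0, and an excess of about 15 patients is lost. This is the extreme case. It does not depend on unblinding.

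**Step 5. Illustration of differential classification (assumed rates).** Let the true rate be b in both arms, and let fractions s1 and s0 of events be classed as AEs. The apparent rates are p1 = b × s1 and p0 = b × s0. The chance of a two-sided 5% significant difference with n = 154 per arm is approximately Φ[(|p1 − p0| − 1.96 × SE0) / SE1]. Here SE0 = √(2p̄(1 − p̄)/n), p̄ is the mean of p1 and p0, and SE1 = √((p1(1 − p1) + p0(1 − p0))/n).

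| b | s1 v s0 | p1 v p0 | ratio | chance of false difference |
|---|---|---|---|---|
| 20% | 50% v 50% | 10% v 10% | 1.00 | 5% (nominal) |
| 20% | 50% v 40% | 10% v 8% | 1.25 | 9% |
| 20% | 60% v 40% | 12% v 8% | 1.50 | 21% |
| 40% | 50% v 40% | 20% v 16% | 1.25 | 15% |
| 40% | 60% v 40% | 24% v 16% | 1.50 | 42% |
| 20% | 40% v 60% | 8% v 12% | 0.67 | 21% |

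For the third row: SE0 = √(2 × 0.10 × 0.90/154) = 0.0342, SE1 = √((0.1056 + 0.0736)/154) = 0.0341, and (0.04 − 1.96 × 0.0342)/0.0341 = −0.79, so Φ = 0.21. Equal classification gives no bias, and the bias can run either way.

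**Step 6. A linked inconsistency.** Safety Assessments ends EA or sham EA when an AE occurs. Criteria for Discontinuing the Allocated Intervention lists only serious adverse events. The classification may therefore also affect how much treatment a patient receives, depending on which section is followed.

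**The case against.** The strongest reply is that blinded assessors record AEs and that the acupuncturists' role is mainly local. A reader might infer that the acupuncturist decides relatedness, or decides whether a systemic event counts. The text does not say so: the second limb names no judge, and expectedness is not assigned to the acupuncturist anywhere. That part of the reply stands.

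A reader might also infer that AE frequencies cannot be compared between arms, or that the trial cannot detect harm from EA. Neither follows. The second limb covers the study procedure as well as EA, so sham events can qualify, and the frequencies are comparable if classification is blinded or equal. The blinded SOFA and day-28 outcomes already show much systemic harm.

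It can further be said that Monitoring and Quality Control provides outside evaluation of safety parameters, audits of at least half the cases and video of more than 30% of sessions, and that a condensed article leaves causality forms to the full protocol. These arrangements help, but the article describes no blinded rating of cause. The point also rests on the stated definition and the stated division of roles, not on detail left out. Blinding would not recover the events that the definition drops in both arms.

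**Conclusion.** The point holds in a limited form. The AE definition makes expectedness and relatedness entry conditions, and the section gives AE assessment to one blinded and one unblinded group without saying whose judgement decides. Sepsis-typical harms outside the SOFA items, organ-support-free days and mortality can be lost in both arms. The comparison of AE frequency is open to bias of unknown size and direction.

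The size cannot be derived from the documents. The figures of 31 v 46 patients recorded as 0 v 0, and of 9% to 42% for a false difference, rest wholly on assumed event and classification rates and serve as illustration only. The differential part further assumes that knowledge of allocation reaches the classification, which the text permits but does not state. The point should be corrected. It does not touch the primary efficacy analysis.

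**What to change.** In Safety Assessments, record three groups of events over the AE period in Table 1 (days 1 to 6), in both arms and whatever their expectedness or cause: all serious events, all needle-site events, and a short pre-listed set of systemic events not already captured as outcomes. Compare these counts by randomised arm. Keep expectedness and relatedness as separate fields on each recorded event. Have relatedness of the systemic events rated by the already blinded ICU physicians, without sight of the needling record, and keep the acupuncturist's view as descriptive.

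Separately, reconcile Safety Assessments with Criteria for Discontinuing the Allocated Intervention on which adverse events end the allocated treatment.

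The cost is wording in the protocol and case report form, and more entries per patient, most of them due to sepsis. No new staff or procedures are needed. Trial Status reports 136 patients already enrolled, so those patients need either chart abstraction or a stated date from which the new recording applies. Against the planned 308, 308 − 136 = 172 patients would still come under the new recording from the outset, unless the trial stops at the interim analysis.
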